# Scale III: Scored Patient-Generated Subjective Global Assessment (PG-SGA)

[figure not shown]

## Scored Patient-Generated Subjective Global Assessment (PG-SGA)

History: Boxes 1 - 4 are designed to be completed by the patient.  
[Boxes 1-4 are referred to as the PG-SGA Short Form (SF)]

### 1. Weight (See Worksheet 1)

In summary of my current and recent weight:

I currently weigh about \_\_\_\_\_ kg

I am about \_\_\_\_\_ cm tall

One month ago I weighed about \_\_\_\_\_ kg

Six months ago I weighed about \_\_\_\_\_ kg

During the past two weeks my weight has:

☐ decreased  ☐ not changed  ☐ increased 

Box 1 ☐

### Patient Identification Information

2. Food intake: As compared to my normal intake, I would rate my food intake during the past month as

- ☐ unchanged   
☐ more than usual   
☐ less than usual 

I am now taking

- ☐ normal food but less than normal amount   
☐ little solid food   
☐ only liquids   
☐ only nutritional supplements   
☐ very little of anything   
☐ only tube feedings or only nutrition by vein 

Box 2 ☐

3. Symptoms: I have had the following problems that have kept me from eating enough during the past two weeks (check all that apply)

- ☐ no problems eating   
☐ no appetite, just did not feel like eating  ☐ vomiting   
☐ nausea  ☐ diarrhea   
☐ constipation  ☐ dry mouth   
☐ mouth sores  ☐ smells bother me   
☐ things taste funny or have no taste  ☐ feel full quickly   
☐ problems swallowing  ☐ fatigue   
☐ pain; where?  \_\_\_\_\_  
☐ other (1)\*\* \_\_\_\_\_  
☐ \*\*Examples: depression, money, or dental problems

Box 3 ☐

### 4. Activities and Function:

Over the past month, I would generally rate my activity as:

- ☐ normal with no limitations   
☐ not my normal self, but able to be up and about with fairly normal activities   
☐ not feeling up to most things, but in bed or chair less than half the day   
☐ able to do little activity and spend most of the day in bed or chair   
☐ pretty much bed ridden, rarely out of bed 

Box 4 ☐

### Worksheet 1 – Scoring Weight Loss

To determine score, use 1-month weight data if available. Use 6-month data only if there is no 1-month weight data. Use points below to score weight change and add one extra point if patient has lost weight during the past 2 weeks. Enter total point score in Box 1 of PG-SGA.

| Weight loss in 1 month | Points | Weight loss in 6 months |
|------------------------|--------|-------------------------|
| 10% or greater         | 4      | 20% or greater          |
| 5-9.9%                 | 3      | 10- 19.9%               |
| 3-4.9%                 | 2      | 6- 9.9%                 |
| 2-2.9%                 | 1      | 2- 5.9%                 |
| 0-1.9%                 | 0      | 0- 1.9%                 |

Numerical score from Worksheet 1 ☐

Additive Score of Boxes 1-4 (See Side 1) ☐ A

### 5. Worksheet 2 – Disease and its relation to nutritional requirements:

Score is derived by adding 1 point for each of the following conditions:

- ☐ Cancer ☐ Presence of decubitus, open wound or fistula  
☐ AIDS ☐ Presence of trauma  
☐ Pulmonary or cardiac cachexia ☐ Age greater than 65  
☐ Chronic renal insufficiency  
Other relevant diagnoses (specify) \_\_\_\_\_

Primary disease staging (circle if known or appropriate) I II III IV Other

Numerical score from Worksheet 2 ☐ B

### 6. Worksheet 3 – Metabolic Demand

Score for metabolic stress is determined by a number of variables known to increase protein & caloric needs. Note: Score fever intensity or duration, whichever is greater. The score is additive so that a patient who has a fever of 38.8 °C (3 points) for < 72 hrs (1 point) and who is on 10 mg of prednisone chronically (2 points) would have an additive score for this section of 5 points.

| Stress          | none (0)           | low (1)                                             | moderate (2)                                                      | high (3)                                             |
|-----------------|--------------------|-----------------------------------------------------|-------------------------------------------------------------------|------------------------------------------------------|
| Fever           | no fever           | > 37.2 and < 38.3                                   | ≥ 38.3 and < 38.8                                                 | ≥ 38.8 °C                                            |
| Fever duration  | no fever           | < 72 hours                                          | 72 hours                                                          | > 72 hours                                           |
| Corticosteroids | no corticosteroids | low dose
(< 10 mg prednisone
equivalents/day) | moderate dose
(≥ 10 and < 30 mg
prednisone equivalents/day) | high dose
(≥ 30 mg prednisone
equivalents/day) |

Numerical score from Worksheet 3 ☐ C

### 7. Worksheet 4 – Physical Exam

Exam includes a subjective evaluation of 3 aspects of body composition: fat, muscle, & fluid. Since this is subjective, each aspect of the exam is rated for degree. Muscle deficit/loss impacts point score more than fat deficit/loss. Definition of categories: 0 = no abnormality, 1+ = mild, 2+ = moderate, 3+ = severe. Rating in these categories is not additive but are used to clinically assess the degree of deficit (or presence of excess fluid).

#### Muscle Status

|                                                 |            |
|-------------------------------------------------|------------|
| temples (temporalis muscle)                     | 0 1+ 2+ 3+ |
| clavicles (pectoralis & deltoids)               | 0 1+ 2+ 3+ |
| shoulders (deltoids)                            | 0 1+ 2+ 3+ |
| interosseous muscles                            | 0 1+ 2+ 3+ |
| scapula (latissimus dorsi, trapezius, deltoids) | 0 1+ 2+ 3+ |
| thigh (quadriceps)                              | 0 1+ 2+ 3+ |
| calf (gastrocnemius)                            | 0 1+ 2+ 3+ |
| Global muscle status rating                     | 0 1+ 2+ 3+ |

#### Fat Stores

|                            |            |
|----------------------------|------------|
| orbital fat pads           | 0 1+ 2+ 3+ |
| triceps skin fold          | 0 1+ 2+ 3+ |
| fat overlying lower ribs   | 0 1+ 2+ 3+ |
| Global fat deficit rating  | 0 1+ 2+ 3+ |
| Fluid status               |            |
| ankle edema                | 0 1+ 2+ 3+ |
| sacral edema               | 0 1+ 2+ 3+ |
| ascites                    | 0 1+ 2+ 3+ |
| Global fluid status rating | 0 1+ 2+ 3+ |

Point score for the physical exam is determined by the overall subjective rating of the total body deficit. No deficit score = 0 points  
Mild deficit score = 1 point  
Moderate deficit score = 2 points  
Severe deficit score = 3 points  
Again, muscle deficit/loss takes precedence over fat loss or fluid excess.

Numerical Score for Worksheet 4 ☐ D

Total PG-SGA Score (Total numerical score of A+B+C+D) ☐

Global PG-SGA Category Rating (Stage A, Stage B or Stage C) ☐

Clinician Signature \_\_\_\_\_ RD RN PA MD DO Other \_\_\_\_\_ Date \_\_\_\_\_

# Scale IV: Patient Health Questionnaire-9 (PHQ-9) Depression Screening Scale

## PATIENT HEALTH QUESTIONNAIRE (PHQ-9)

ID #: \_\_\_\_\_ DATE: \_\_\_\_\_

Over the last 2 weeks, how often have you been bothered by any of the following problems?  
(use "✓" to indicate your answer)

|                                                                                                                                                                             | Not at all | Several days | More than half the days | Nearly every day |
|-----------------------------------------------------------------------------------------------------------------------------------------------------------------------------|------------|--------------|-------------------------|------------------|
| 1. Little interest or pleasure in doing things                                                                                                                              | 0          | 1            | 2                       | 3                |
| 2. Feeling down, depressed, or hopeless                                                                                                                                     | 0          | 1            | 2                       | 3                |
| 3. Trouble falling or staying asleep, or sleeping too much                                                                                                                  | 0          | 1            | 2                       | 3                |
| 4. Feeling tired or having little energy                                                                                                                                    | 0          | 1            | 2                       | 3                |
| 5. Poor appetite or overeating                                                                                                                                              | 0          | 1            | 2                       | 3                |
| 6. Feeling bad about yourself—or that you are a failure or have let yourself or your family down                                                                            | 0          | 1            | 2                       | 3                |
| 7. Trouble concentrating on things, such as reading the newspaper or watching television                                                                                    | 0          | 1            | 2                       | 3                |
| 8. Moving or speaking so slowly that other people could have noticed. Or the opposite — being so fidgety or restless that you have been moving around a lot more than usual | 0          | 1            | 2                       | 3                |
| 9. Thoughts that you would be better off dead, or of hurting yourself                                                                                                       | 0          | 1            | 2                       | 3                |

add columns  +  +

(Healthcare professional: For interpretation of TOTAL, TOTAL:   
please refer to accompanying scoring card).

## Scale V: Distress Thermometer (DT) Psychological Screening Tool

**Distress** is an unpleasant experience of a mental, physical, social, or spiritual nature. It can affect the way you think, feel, or act. **Distress** may make it harder to cope with having cancer, its symptoms, or its treatment.

**Instructions:** Please circle the number (0–10) that best describes how much distress you have been experiencing in the past week, including today.

**Extreme distress**

**No distress**

A vertical thermometer scale with numbers 0 through 10. The scale is marked with horizontal lines for each integer. The top of the thermometer has a bulb with radiating lines, and the bottom has a bulb. The scale is enclosed in a rounded rectangular frame.

## Scale 6: Hospital Anxiety and Depression Scale (HADS)

Instructions: Emotions play a significant role in most illnesses. If healthcare providers understand your emotional state, they can offer better support. Please read each statement below and check ( ✓ ) the response that best describes how you have felt over the past month. Do not overthink your answers—your immediate response is likely more accurate.

1. I feel tense or wound up: (     )
  - ① Almost all the time
  - ② Most of the time
  - ③ Sometimes
  - ④ Not at all
2. I still enjoy the things I used to enjoy: (     )
  - ① Definitely as much
  - ② Not quite as much
  - ③ Only a little
  - ④ Hardly at all
3. I get a sort of frightened feeling, as if something awful might happen: (     )
  - ① Very definitely and quite badly
  - ② Yes, but not too badly
  - ③ A little, but it doesn't worry me
  - ④ Not at all
4. I can laugh and see the funny side of things: (     )
  - ① As much as I always could
  - ② Not quite so much now
  - ③ Definitely not so much now
  - ④ Not at all
5. Worrying thoughts go through my mind: (     )
  - ① A great deal of the time
  - ② A lot of the time
  - ③ From time to time, but not too often
  - ④ Only occasionally
6. I feel cheerful: (     )
  - ① Not at all
  - ② Not often
  - ③ Sometimes
  - ④ Most of the time
7. I can sit at ease and feel relaxed: (     )
  - ① Definitely
  - ② Usually
  - ③ Not often
  - ④ Not at all
8. I have lost interest in my appearance: (     )
  - ① Definitely
  - ② I don't take as much care as I should

③ I may not take quite as much care

④ I take just as much care as ever

9. I feel restless, as if I have to be on the move: (       )

① Very much indeed

② Quite a lot

③ Not very much

④ Not at all

10. I look forward with enjoyment to things: (       )

① As much as I ever did

② Rather less than I used to

③ Definitely less than I used to

④ Hardly at all

11. I get sudden feelings of panic: (       )

① Very often indeed

② Quite often

③ Not very often

④ Not at all

12. I feel as if I'm slowing down: (       )

① Nearly all the time

② Very often

③ Sometimes

④ Not at all

13. I have a feeling of dread, as if something bad is about to happen to my body: (       )

① Not at all

② Sometimes

③ Very often

④ Most of the time

14. I can enjoy a good book, radio, or TV program: (       )

① Often

② Sometimes

③ Not often

⑤ Very seldom

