➤ **Intervention Strategies**

● **Anti-Cancer Treatment Regimen**

All enrolled patients received radiotherapy delivered in daily fractions of 1.8 - 2.2 Gy, administered five times per week for 6 - 6.5 weeks, resulting in a total tumor dose of 60 - 72 Gy. The clinical target volume and organs at risk were delineated in accordance with consensus guidelines. Concurrent chemotherapy consisted of cisplatin 100 mg/m^2 every 3 weeks.

● **Intervention Measures for the Usual Care Group**

In the control group, based on the patients' questionnaire results, the radiation oncologist and risk-stratified nurses would provide dietary or psychological guidance or recommend appropriate outpatient clinics (nutrition, psychology, or rehabilitation) for patients to seek further consultation. Patients had the autonomy to decide whether or not

to schedule appointments at the recommended outpatient clinics. This reflects the routine medical practice commonly experienced by patients undergoing radiotherapy in China.

- **Intervention Measures for the SHINE-MDT Group**

In the experimental group, patients would be treated with SHINE-MDT in addition to standard anti-oncologic treatment. The SHINE-MDT model with a fixed-site and fixed-membership organizational framework. The team consisted of specialists from radiation oncology, medical oncology, psychology, nutrition, rehabilitation, and nursing, with each discipline maintaining  $\geq 3$  core members. At least one representative from each key department attended every meeting. This team provided direct and prompt nutritional, psychological, and rehabilitation interventions tailored to the patient's needs. All departments participated consistently, facilitating mutual learning and collaborative decision-making.

- **Questionnaires Assessments**

Assessments were conducted through a series of questionnaire surveys, which included the European Organization for Research and Treatment of Cancer (EORTC) Quality-of-life Questionnaire Core 30 (EORTC QLQ-C30) and Head and Neck Cancer Module (EORTC QLQ-H&N35), NRS 2002, PG-SGA, DT, PHQ-9, and HADS. The PHQ-9 and HADS were evaluated every two weeks from radiotherapy initiation through the first-month post-treatment, while the other questionnaires were assessed weekly.

- **Frequency of Questionnaire Assessment**

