| Patient-Generated Subjective Global Assessment (PG-SGA) | Baseline (pre-radiotherapy) and weekly from radiotherapy initiation through the first-month post-treatment, followed by evaluations at 2, 3, and 6 months post-treatment.               |
| Distress Thermometer (DT)                               | Baseline (pre-radiotherapy) and weekly from radiotherapy initiation through the first-month post-treatment, followed by evaluations at 2, 3, and 6 months post-treatment.               |
| Patient Health Questionnaire-9 (PHQ-9)                  | Baseline (pre-radiotherapy) and once every two weeks from radiotherapy initiation through the first-month post-treatment, followed by evaluations at 2, 3, and 6 months post-treatment. |
| Hospital Anxiety and Depression Scale (HADS)            | Baseline (pre-radiotherapy) and once every two weeks from radiotherapy initiation through the first-month post-treatment, followed by evaluations at 2, 3, and 6 months post-treatment. |

- Quality control of questionnaire evaluations

To standardize questionnaire evaluations, we utilized video tutorials to assist patients in better understanding the self-rating questionnaires (EORTC QLQ-C30, EORTC QLQ-

H&N35, PG-SGA, DT, PHQ-9, HADS), enabling more accurate survey completion. For examiner-rated questionnaires (NRS 2002), nurses underwent collective training on the questionnaire content. They then conducted evaluations using standard patients to identify scoring discrepancies among different questionnaire-assessed nurses. This process enhanced understanding of the questionnaire content and reduced errors in examiner ratings.

For nutritional interventions, patients with an NRS 2002 score below 3 and a PG-SGA score below 4 were classified as having no or mild malnutrition. These patients received dietary guidance while continuing scheduled radiotherapy. For patients with a PG-SGA score of 4 or higher, different approaches were taken: those in the control group were referred to the nutrition department for consultation. In contrast, patients in the experimental group were coordinated by the risk-stratified nurses to receive individualized treatment from SHINE-MDT.

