For psychological interventions, patients with mild or no psychological disorders (DT score < 4, PHQ-9 score < 10, and both HADS-A and HADS-D scores < 8) continued scheduled radiotherapy. When a patient met any of the following criteria: 1) the DT score  $\geq 4$ , 2) the PHQ-9 score  $\geq 10$ , 3) the HADS-A or HADS-D score  $\geq 8$ , the risk-stratified nurses recommended that patients in the UC group go to the mental health center for psychological counseling, while the risk-stratified nurses coordinated patients in the SHINE-MDT group to receive appropriate treatment from SHINE-MDT. Patients in the control group maintained in their assigned group throughout the study.

- Research Intervention Procedure

[figure not shown]

eFigure1: Research Intervention Procedure

abbreviation: SHINE-MDT: Supportive Holistic Interventions by Nurses and Experts via Multidisciplinary Team

- Nutritional and Psychological Intervention Process for the Usual Care Group

[figure not shown]

eFigure 2: Nutritional Intervention Process for the Usual Care Group

abbreviation: ONS: Oral Nutritional Supplements; PPN: Partial Parenteral Nutrition

[figure not shown]

eFigure 3: Psychological Intervention Process for the Usual Care Group; HADS-A: HADS-Anxiety; HADS-D: HADS-Depression

- Nutritional and Psychological Intervention Process for the SHINE-MDT

[figure not shown]

eFigure 4: Nutritional Intervention Process for the SHINE-MDT Group

abbreviation: SHINE-MDT: Supportive Holistic Interventions by Nurses and Experts via Multidisciplinary Team; ONS

: Oral Nutritional Supplements; PPN: Partial Parenteral Nutrition

[figure not shown]

eFigure5: Psychological Intervention Process for the SHINE-MDT Group

abbreviation: SHINE-MDT: Supportive Holistic Interventions by Nurses and Experts via Multidisciplinary Team;

HADS-A: HADS-Anxiety; HADS-D: HADS-Depressions

- Rehabilitation Intervention Process for the SHINE-MDT

Rehabilitation Physician: participates in MDT discussions, leads the patient's functional assessment, and formulates the rehabilitation prescription.

Specialized rehabilitation therapists then implement interventions if needed:

Speech Pathologist (SP): Addresses dysarthria, dysphonia, and dysphagia through articulation training, voice function rehabilitation, and swallowing therapy.

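### The HADS form asks about the past month but is given every two weeks, so on-treatment scores can lag or dilute early change

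*Protocol*

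**What the plan says.** The recall period is set by the instruction at the head of Scale 6 in Appendix 5, which asks for "the response that best describes how you have felt over the past month".

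The schedule is set twice. Section 3.2 (Questionnaires Assessments) states: "The PHQ-9 and HADS were evaluated every two weeks from radiotherapy initiation through the first-month post-treatment". The HADS row of eTable 1 gives a baseline assessment, then "once every two weeks from radiotherapy initiation through the first-month post-treatment, followed by evaluations at 2, 3, and 6 months post-treatment".

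The protocol uses the scores in two ways. HADS is one of three measures of psychological status (sections 2 and 4.4), a secondary objective. It also guides care: the psychological intervention paragraph of section 3.2 lets patients continue as scheduled when, among other conditions, "both HADS-A and HADS-D scores < 8" holds. It starts referral (usual care) or team care (SHINE-MDT) when any one criterion is met: DT of 4 or more, PHQ-9 of 10 or more, or "the HADS-A or HADS-D score" of 8 or more.

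The two companion scales read differently. PHQ-9, on the same two-week schedule as HADS, begins "Over the last 2 weeks, how often have you been bothered by any of the following problems". The DT, given weekly, asks about the past week including today.

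**The concern.** A score collected every two weeks should describe roughly the two weeks since the previous one. With a one-month recall it also covers time the previous form has already covered. At week 2 it covers time before radiotherapy and, in the SHINE-MDT group, before team care during radiotherapy could have had any effect.

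Two uses of HADS are exposed. For the secondary outcome, an early difference between groups may appear smaller or later than it was, and a change from baseline to week 2 compares two overlapping periods. For the care criterion, new symptoms may be averaged with an earlier, calmer period, and a patient who has improved may still report what preceded the improvement. Anxiety and depression are part of the trial's rationale (section 1). Among the three trigger instruments, HADS-A is the only dedicated anxiety scale. The two-week phase is also when the intervention is delivered.

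The answers cannot be corrected for this in the analysis, because a shorter recall cannot be recovered from a form that asked about a longer one.

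**Working it through.** The protocol gives no figure for HADS precision or effect that could be reproduced. Its sample size of 214 rests on the interruption rate and does not involve HADS. The check is therefore of windows against intervals.

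**Inputs**
- Recall period W: one month (Scale 6), taken as 28, 30 or 31 days.
- Interval I: 14 days (section 3.2, eTable 1).
- Start of radiotherapy: day 0.

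**Overlap of consecutive windows**, (W − I)/W:
- W = 28: 14/28 = 50%
- W = 30: 16/30 = 53%
- W = 31: 17/31 = 55%

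**Share of a window before radiotherapy**, max(0, W − t)/W, for an assessment on day t:
- Day 14: the same arithmetic as above, 50% to 55%. With W = 30, 16 of the 30 days.
- Day 28: 0/28 = 0%, 2/30 = 7%, 3/31 = 10%.

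The reach back before treatment is thus largely a week-2 problem. The overlap between neighbours persists through the two-week phase.

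**How long that phase lasts.** Radiotherapy runs 6 to 6.5 weeks (section 3.2) and the phase continues for one month more, so it contains about five assessments after the start: weeks 2, 4, 6, 8 and 10.

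**Later visits.** The 1, 2, 3 and 6 month visits are nominally a month or more apart, so their windows do not overlap. The ±3-day visit windows could bring two neighbouring monthly visits up to 6 days closer, at most 6/30 = 20% in an extreme case, which is not material.

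**Companion scales**

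| Scale | Recall | Interval on treatment | Overlap |
|---|---|---|---|
| HADS | one month | 2 weeks | 50–55% |
| PHQ-9 | 2 weeks | 2 weeks | 0% |
| DT | 1 week | 1 week | 0% |

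**Illustration of dilution (assumption, not a result).** If patients weighted every day of a 30-day window equally, a constant difference beginning on day 0 would show at 14/30 = 47% of its size at week 2 (14/28 = 50% to 14/31 = 45% for the other month lengths). If they answered only for recent days, it would show at 100%. The documents do not say where between these patients fall, so no single figure can be claimed.

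**The case against.** **The effect may be small.** The items are in the present tense and the form discourages long reflection, so patients may answer mainly for recent days. Both groups complete the same form, so no bias between groups is shown, only possible attenuation early on. This stands, and it is why the dilution is not quantified.

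**Care does not depend on HADS alone.** Any one criterion suffices, and DT (weekly) and PHQ-9 (two-weekly) cover recent change. This largely stands: a claim that care is generally delayed would go too far. What remains is that neither of the other two is a dedicated anxiety scale.

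**Long recall is not unique to HADS.** The weekly PG-SGA has past-month questions, and NRS 2002 looks at weight loss over one to three months. True, so the contrast is with the other psychological scales only. It does not remove the mismatch for HADS.

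**The wording may be a translation.** Appendix 5 is headed as an English version, and the form used in China may read differently. This deserves a check first, but the protocol as written contains the mismatch.

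**A stronger reading is tempting.** Option 1 is the worst answer in some items ("① Almost all the time", item 1) and the best in others ("① Definitely as much", item 2), and no score values are printed. A reader might infer that the form cannot produce the HADS-A and HADS-D scores to which the cut-off of 8 applies. The documents do not support that. The circled numerals are option labels: the ECOG item in the same appendix uses label 1 for value 0. Patients are told to tick an answer, and nothing says that labels are added. If the fourteen items split seven and seven (an assumption), scoring each from 0 to 3 by its direction gives subscales from 0 to 7 × 3 = 21, on which a cut-off of 8 works. A scoring key may sit in documents not shown. The label 5 on the last option of item 14 is a clerical check only.

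**Conclusion.** The point holds as a mismatch between the printed recall period and the schedule. During radiotherapy and the first month after it, consecutive HADS windows share 50% to 55% of their days, and about half of the week-2 window precedes radiotherapy. This rests only on reading a month as 28 to 31 days and on visits taking place as scheduled.

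The consequence is one of direction: on-treatment HADS scores can lag or dilute early change. Its size cannot be derived from the documents. It concerns one of several psychological measures and one of several care triggers. The primary endpoint, the sample size and, at their nominal dates, the 2, 3 and 6 month visits are untouched. Neither a bias between groups nor a form that cannot be scored against the cut-off follows from what the protocol says.

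**What to change.** First check the recall wording in the language version that patients complete. If it is also one month, reconcile it with the two-week schedule so that the recall period does not exceed the interval between assessments. Changing the wording leaves the schedule and the care criteria as they are. Check the label of item 14's last option on the same page.

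The protocol describes its procedures largely in the past tense, so forms may already be in use. In that case:
- flag each HADS record by form version;
- report on-treatment scores from the present form as one-month recall;
- do not interpret the week-2 score as reflecting only time on treatment.

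The cost is one form page. The drawback is that early and later forms may differ. Introducing the new page with newly enrolled patients, rather than in the middle of a patient's course, avoids an artificial break within individual series.
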